#### Objective one: inter-reliability analysis.

The mode effect (phone v. in-person) of the rapid phone-based HFA compared to the comprehensive in-person HFA will be analyzed using the “directly mapped” survey items. The results will be analyzed and reported in three ways: as a simple percent agreement of responses, using the Cohen’s Kappa to account for the percent of agreement that is expected by chance, and using a prevalence and bias adjusted kappa (PABAK) to account for prevalence and bias in the sample. Calculating PABAK is especially important for a HFA, where many of the survey items are expected to be available and therefore, the expected agreement by chance for many indicators is high due to high prevalence [26].

Taken together, these three measures will provide a nuanced understanding of the results [27].

There are some differences on what is considered adequate for reliability. While literature suggests that a Kappa coefficient larger than 0.61 would be reliable, it is acknowledged that these thresholds can be somewhat arbitrary. To address this, a scale for the level of agreement [28] will be used: almost perfect agreement above 0.90, strong 0.80 to 0.90, moderate 0.60 to 0.79, weak 0.40 to 0.59, and minimal 0.20 to 0.39.

#### Objective two: concurrent criterion validity analysis.

This objective focuses on concurrent criterion validity – the extent to which a new measurement technique agrees with a gold standard when the assessments are undertaken at approximately the same time. Both the “directly mapped” and the “indirectly mapped” indicators will be dichotomized to understand the differences in the results between the two surveys with the comprehensive in-person HFA being the gold standard. Sensitivity and specificity will be used to assess whether each indicator meets the predefined validation threshold of 0.7. This has been chosen as the validation threshold because of the specific intent to use low cost, high frequency surveys to generate timely signals as a complement to, rather than replacement for, periodic in-person surveys which are still needed for their depth, comprehensiveness, and rigor. We will also compare results stratified by direct versus indirect indicators and by survey domain (e.g., infrastructure, human resources) to identify any differences.

In addition, regression analysis will be conducted to assess whether sensitivity and specificity are associated with any of the seven domains of the rapid phone-based HFA, facility characteristics, respondent characteristics and potentially enumerator characteristics and timing between the two surveys. Sensitivity checks will also be conducted to see if the duration of time between the two surveys is correlated with the discordant answers.

Regression analysis will also be conducted to identify any variations in the findings that can be attributed to facility characteristics. Subgroup analysis will be conducted based on (1) oblast, (2) rural versus urban, and (3) facility type to identify if any underlying, facility characteristics influence the reliability and validity of the rapid, phone-based HFA results. This will identify whether validity is different in particular sub-groups. For example, the rapid, phone-based HFA may have improved validity in smaller facilities where one respondent is likely to be familiar with all the tracer items and could be more challenging in a larger facility with multiple departments.

Finally, we will compare if the reliability and validity of the rapid phone-based HFA changes based on the order of survey administration. For example, recently conducting the in-person survey may improve the consistency of the responses in the phone survey such that respondents have been primed to respond based on their recent verification of the survey items.

#### Objective three: non-response rate.

Although both surveys will initially include the same sample of 500 facilities, we expect that the final samples for each HFA will differ in the end due to varying non-response rates. A simple-t test will be used to assess whether there is a significant difference in the response rates between the rapid phone-based HFA and the comprehensive in-person HFA. Balance tests will also be used to assess whether the characteristics of the final sample of included facilities (the original sample plus any replacements) for the comprehensive in-person HFA and the rapid phone-based HFA sample remain similar across both surveys. Finally, we will document any issues with phone service coverage and the ownership of mobile phones by facilities and respondents, as well as any reported instances of costs to the recipient.

In case a significant difference is found in response rate or sample characteristics, regression analysis will be used to assess associations with discordance in survey completion. This will be done by creating a binary variable to indicate whether the comprehensive in-person HFA was completed in a health facility, while the rapid phone-based HFA wasn’t. This binary variable will then regressed on facility characteristics and whether the rapid phone-based HFA was initiated before or after the comprehensive in-person HFA. Since the non-response rate is expected to be higher for the rapid phone-based HFA, this analysis will only be done for health facilities which complete the comprehensive in-person HFA but not the rapid phone-based HFA.

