#### Sampling.

The sampling methodology for both surveys is designed to be representative of the PHC health facilities in Tajikistan at the national and oblast (region) levels. Since the role of private sector in providing PHC services is minimal in Tajikistan, the sample frame consists of all public PHC health facilities in the country comprising of- City and District Health Centers (family medicine departments), Rural Health Centers, and Health Houses. The sample was stratified across all oblasts. To obtain quality results from the comparison of the rapid phone-based HFA and the comprehensive in-person HFA, each survey will be conducted in the identical sample of 500 facilities described in Table 2.

**Table 2 pone.0309570.t002:** Sample for the rapid-phone based and comprehensive in-person HFAs.

		# Facilities	# Selected
Oblast	Dushanbe	15	15
	Sughd	616	151
	Khaktlon	1,123	150
	Gorno-Badakhshan Autonomous Region	227	84
	Districts of Republican Subordination	713	100
Type	City Health Center	41	41
	District Health Center	53	53
	Rural Health Center	895	214
	Health House	1,705	192
**TOTAL**		**2,694**	**500**
		

The enumerators will obtain verbal consent for the rapid phone-based HFA and written consent for the comprehensive in-person HFA from the respondents before starting the survey. If a respondent declines to participate, the reason for their refusal will be documented, and the facility will be replaced by a facility from the same strata whenever available. In the event of a non-response, health facilities will be replaced from a “replacement list” curated from the sample frame for each survey, following the same protocol of random sampling selection. Furthermore, in the event of a non-response, replacements for the two surveys will be done independently. This means that if a facility does not participate in the rapid phone-based HFA and needs to be replaced with another health facility, it will not be simultaneously replaced in the comprehensive in-person HFA, and vice-versa, unless the non-participation is due to the closure of the facility. As a result, the final samples may differ slightly due to varying response rates.

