#### Timing of survey administration.

The comprehensive in-person HFA and the rapid phone-based HFA will be conducted as close in timing as possible, ideally within a two-week period for each health facility. The close timing of the surveys minimizes the risk of external factors (for example, a health facility receiving new medical supplies) impacting the data recorded in each survey and will ensure a more reliable comparison. However, there is a risk that conducting both surveys too close will introduce respondent fatigue that might affect results. Therefore, the order of the surveys for each health facility will be randomized to control for some of the real changes that may occur due to the order, with 50% of facilities receiving the rapid phone-based HFA first and 50% of the facilities receiving the comprehensive in-person survey first. This will allow for a more robust analysis. It will also allow us to conduct a longitudinal analysis of responses for the rapid phone-based HFA and the comprehensive in-person HFA in each facility to identify possible confounding effects depending on which survey the facility receives first. We would expect this to be a possibility especially in facilities that receive the in-person survey first, as respondent recall may be primed by the recent in-person verification of survey items and therefore, respondents may answer the rapid phone-based HFA with greater validity.

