More broadly, findings from this study will be used to provide measurement and methodological guidance for HFAs. The findings will provide novel insights on the complementarities of various methods, which HFA domains and sub-domains can be administered via phone with high reliability and validity, and which HFA domains are likely to require in-person administration or other verification approaches. It is possible that the findings could be robust enough to generate correction factors for phone-based surveys that can be applied to approximate in-person measures in contexts where traditional data collection approaches are not possible (such as during health emergencies or conflict-impacted areas). Finally, the findings on response rates will be published to inform future implementation guidance on the feasibility of different methods of data collection given HFA operational constraints and measurement needs in different contexts and when each method is likely to be particularly useful.

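### Objective 3 pools first and second approaches in a single phone versus in-person response comparison, and no analysis that always runs shows response by randomised order

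*Protocol article*

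**What the plan says.** Under Sampling, the protocol article says that "each survey will be conducted in the identical sample of 500 facilities described in Table 2", so every facility is approached twice. Under Timing of survey administration, the two surveys are to fall close together, "ideally within a two-week period for each health facility", in random order, "with 50% of facilities receiving the rapid phone-based HFA first and 50% of the facilities receiving the comprehensive in-person survey first". The same section warns that "there is a risk that conducting both surveys too close will introduce respondent fatigue that might affect results" and expects order effects mainly where the in-person survey comes first, through priming of recall.

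The section on Objective three fixes the comparison: "A simple-t test will be used to assess whether there is a significant difference in the response rates" between phone and in-person. It mentions no split by order. Order appears there once, as a covariate in a follow-up model with a condition attached: "In case a significant difference is found in response rate or sample characteristics, regression analysis will be used". The outcome of that model is the pattern of in-person completed and phone not completed, and the section limits the analysis to facilities with that pattern.

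The other planned look at order stands at the end of the Objective two section and concerns different outcomes: "we will compare if the reliability and validity of the rapid phone-based HFA changes based on the order of survey administration". On use of the results, Strengths and limitations says that "the findings on response rates will be published to inform future implementation guidance on the feasibility of different methods of data collection".

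**The concern.** Willingness to take part in a second survey within about two weeks may depend on having just been asked for the first. Fatigue would lower response to the second approach and familiarity would raise it. The two modes place different burdens on a facility: a call of 30 to 45 minutes that needs no preparation, against a visit preceded by an advance questionnaire drawn from facility records. Equal carry-over in both directions is therefore possible but should not be taken for granted.

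Randomising the order balances position between the modes. It does not remove carry-over from the pooled difference. The protocol recognises order effects and randomises order to examine them, yet for response, which belongs to one of its three primary objectives, it commits to no analysis by order that always runs. A reader of the published rates could not tell whether the difference reflects the modes or partly the sequence in which they were fielded.

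**Working it through.** **Inputs from the protocol article.** 500 facilities per survey, the same ones; order 50:50, so 500 × 0.5 = 250 first and 250 second approaches per mode. There is no stated response rate, shift or detectable difference for Objective 3, so there is no figure of the plan's own to reproduce. All rates and shifts below are assumptions.

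**Step 1: bias of the pooled difference.** Let p1 and p2 be phone response when first and second, and q1 and q2 the same for in-person.

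- Pooled difference = (p1 + p2)/2 − (q1 + q2)/2
- First-approach difference = p1 − q1
- Pooled minus first-approach = [(p2 − p1) − (q2 − q1)]/2

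| Phone shift when second | In-person shift when second | Pooled minus first-approach |
|---|---|---|
| −5 | −5 | 0 |
| −5 | 0 | −2.5 points |
| −10 | 0 | −5 points |
| −15 | 0 | −7.5 points |
| +5 | 0 | +2.5 points |
| +5 | −5 | +5 points |

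In the last row, first-approach rates of 90% (phone) and 95% (in-person) give a pooled difference of −5 + 5 = 0, so a real difference is masked. In the other direction, take no first-approach difference and a phone-only shift of −5 points. The pooled test (500 per mode, two-sided 0.05, treated as independent samples) is then significant with probability about 0.24 at a rate of 90% and 0.37 at 95%. For a shift of −10 points the probabilities are about 0.67 and 0.85.

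**Step 2: does the follow-up regression cover this?**

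- It runs only if response rates or sample characteristics differ significantly.
- It models one pattern, in-person complete and phone not, so the reverse pattern is not examined.
- As written it includes only facilities with that pattern. The binary outcome is then 1 for every facility and no order coefficient can be estimated.
- It would leave the reported rate difference unchanged in any case.

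**Step 3: price of looking at first approaches only.** Half-width = 1.96 × √{[p(1 − p) + q(1 − q)]/n}, with in-person at 95%:

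| Phone rate | Half-width, n = 500 | Half-width, n = 250 | Power, n = 500 | Power, n = 250 |
|---|---|---|---|---|
| 85% | 3.7 points | 5.2 points | >0.99 | 0.96 |
| 90% | 3.3 points | 4.6 points | 0.85 | 0.57 |

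At 85% versus 95% the sum of the two variances is 0.1275 + 0.0475 = 0.175. The squared standard errors are 0.175/250 = 0.00070 and 0.175/500 = 0.00035. First approaches alone have the smaller mean squared error only if (shift/2)² > 0.00035, that is, if the differential shift exceeds 2 × √0.00035 = 3.7 points.

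**Step 4: precision of the mode-by-order contrast.** (p2 − p1) − (q2 − q1) = (p2 + q1) − (p1 + q2), which compares the mean number of surveys completed per facility between the two randomised orders. Under the same rates, with independence within facility, its half-width is 1.96 × √(2 × 0.175/250) = 7.3 points. For the bias, which is half the contrast, that is 3.7 points. Positive correlation within facility would widen both.

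**The case against.** Several points on the other side stand.

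- **Evidence.** The size and direction of carry-over are unknown. The fatigue warning concerns results in general, and the order discussion concerns priming of answers; neither states that participation will change. The causes of phone non-response that the article names are mostly unrelated to order: connectivity, time, and the ease of not answering. Official letters, at least five call attempts and rescheduled visits may also limit any effect.
- **Target.** The article does not promise stand-alone rates. It describes a phone survey repeated over time on a panel, as a complement to in-person assessments, so respondents will often have been surveyed before. An order-balanced average is a defensible headline.
- **Cost.** A first-approach comparison loses precision, as Step 3 shows, and gives up the within-facility comparison that the identical sample allows.
- **Level of detail.** A table by order is ordinary analysis-plan content, and that plan is not shown. But the article does not leave order in Objective 3 open: it assigns it to a conditional regression, and that choice can be judged as it stands.

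Three stronger readings are tempting, and the documents do not support them. A reader might infer that a non-significant response test means order is never examined; the trigger also includes a difference in sample characteristics. A reader might infer that first approaches are free of contamination. In fact network managers are told of both surveys beforehand, and in-person teams contact facilities and share the advance questionnaire two weeks ahead, so a phone-first call may follow that contact. Finally, a reader might infer that the pooled comparison is wrong and must give way to the first-approach one. That is a trade of bias against variance that depends on an unknown shift.

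The regression restriction may also be loosely worded, meaning only that the opposite pattern is not modelled. On that reading an order effect could be estimated, but still only after a significant result and for one pattern.

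**Conclusion.** The concern holds in a limited form. The pooled response difference carries half of any differential carry-over, and nothing in the plan that always runs would reveal it. The size is unknown: zero if the shifts are equal, 2.5 to 7.5 points under assumed one-sided shifts of 5 to 15 points. The algebra needs only the 1:1 order; every numerical size rests on assumed rates and shifts, and the power and interval figures also on treating the samples as independent. The defect lies in making the order analysis conditional and, as written, inestimable. Using a pooled headline is not itself an error.

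**What to change.** In the Objective three section, for the original 500 facilities:

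1. Report response and dropout by mode and randomised order, whatever the overall test shows.
2. Report the mode-by-order contrast with its confidence interval. It should be read as an estimate and not used to choose between the two differences, because its half-width is about 7 points under the rates assumed above.
3. Give the first-approach difference (about 250 phone-first versus 250 in-person-first facilities) beside the pooled difference, as a pre-specified sensitivity estimate. Keep the pooled contrast as the headline.
4. State that first approaches are not fully stand-alone, because managers hear of both surveys and in-person teams contact facilities two weeks ahead.

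If the discordance regression is kept, its analysis set must include facilities without the pattern so that the outcome varies.

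The cost is wording and one extra table. Order is randomised and survey completion is already needed for Objective 3, so no new data are required. The first-approach estimate will be less precise, for example a half-width of 5.2 instead of 3.7 points at 85% versus 95%.

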## Abstract

Health facility assessments provide important data to measure the quality of health services delivered to populations. These assessments are comprehensive, resource intensive, and periodic to inform medium- to-longer-term policies. However, in absence of other reliable data sources, country decision makers often rely on outdated data to address service delivery challenges that change more frequently. High-frequency phone surveys are a potential option to improve the efficiency and timeliness of collecting time-sensitive service delivery indicators in-between comprehensive in-person assessments. The objectives of this study are to assess the reliability, concurrent criterion validity, and non-response rates in a rapid phone-based health facility assessment developed by the Global Financing Facility’s FASTR initiative compared to a comprehensive in-person health facility assessment developed by the World Bank’s Service Delivery Indicators Health Program. The in-person survey and corresponding in-person item verification will serve as the gold standard. Both surveys will be administered to an identical sample of 500 health facilities in Tajikistan using the same data collection entity. To assess reliability, percent agreement, Cohens Kappa, and prevalence and bias adjusted Kappa will be calculated. To assess concurrent criterion validity, sensitivity and specificity will be calculated, with a cut-off of.7 used for adequate validity. The study will further compare response rates and dropout rates of both surveys using simple t-tests and balance tests to identify if the characteristics of the phone-based and in-person survey samples are similar after accounting for any differences in survey response rates. The results of this study will provide important insights into the reliability and validity of phone-based data collection approaches for health facility assessments. This is critical as Ministries of Health seek to establish and sustain more continuous data collection, analysis, and use of health facility-level data to complement periodic in-person assessments to improve the quality of services provided to their populations.

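### Objective 3 does not use the facility pairing when it compares response rates, and its balance test on overlapping, refilled samples has little power to show selective phone non-response

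*Protocol article*

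**What the plan says.** The Sampling section of the protocol article states that "each survey will be conducted in the identical sample of 500 facilities described in Table 2". When a respondent declines, "the facility will be replaced by a facility from the same strata whenever available", and "replacements for the two surveys will be done independently", except where a facility has closed.

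The section on Objective three then sets out three steps.

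1. Response rates: "A simple-t test will be used to assess whether there is a significant difference in the response rates" between the two surveys. The Abstract covers dropout as well: "The study will further compare response rates and dropout rates of both surveys using simple t-tests and balance tests". Neither place says whether the test is paired.
2. Sample characteristics: "Balance tests will also be used to assess whether the characteristics of the final sample of included facilities (the original sample plus any replacements") are alike in the two surveys.
3. If response rates or sample characteristics differ significantly, a regression of a binary indicator (in-person completed, phone not) on facility characteristics and survey order. The section expects more non-response by phone. It says the analysis is confined to facilities that completed the in-person survey but not the phone survey.

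The article gives no expected response rates, no significance level and no detectable difference for this objective.

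**The concern.** Each facility in the original sample has two binary results, answered by phone or not and answered in person or not, usually through the same officer-in-charge. A test that ignores this uses the wrong standard error.

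The balance test raises the larger problem. Selective phone non-response shows in which of the original 500 facilities failed to answer. The plan first fills those gaps from the same stratum, and then compares two samples made up mostly of the same facilities. Where replacement succeeds, imbalance on the stratum variables is removed by construction. On other traits, the shared facilities cancel out of the difference while an ordinary two-sample test still counts them in its standard error.

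Objective 3 is one of three primary objectives. The study objectives section justifies it by the need to identify potential biases, and the Strengths and limitations section says the response-rate findings will inform implementation guidance. A falsely reassuring statement that the samples are similar would be carried into that guidance.

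**Working it through.** There is no figure in the plan to reproduce. From the article: 500 facilities approached by both surveys (Table 2; the oblast rows and the type rows each sum to 500), same-stratum replacement, independent replacement lists. Assumed: two-sided 5% level, all response rates, the within-facility correlation, and a facility trait with the prevalence stated.

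**1. Balance test with no selection.** If the two final samples of n = 500 share m facilities, only n − m in each contribute to the difference in means. Its true variance is 2σ²(n − m)/n², while a two-sample test assumes 2σ²/n, so the true standard error is √(1 − m/n) times the assumed one. With phone response 85% and in-person 95%, independent of each other, m ≈ 500 × 0.85 × 0.95 = 404. The factor is √(1 − 0.8075) = 0.439. The critical value 1.96 becomes 1.96/0.439 = 4.47 true standard errors, so the rejection rate is about 0% instead of 5%. Simulation (2,000 runs) gave 0.0%.

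**2. Balance test with selection.** Take a trait with 50% prevalence that does not define the strata, phone response 90% with the trait and 80% without, in-person 95%.
- Trait share in the final phone sample (replacements must also answer): 0.5 × 0.90/0.85 = 0.529, against 0.500 in person. Expected difference 0.029.
- Assumed standard error √(2 × 0.25/500) = 0.0316; difference needed 1.96 × 0.0316 = 0.062.
- True standard error 0.0316 × 0.439 = 0.0139. Power ≈ 1 − Φ((0.062 − 0.029)/0.0139) ≈ 1%. Simulation: 1.2%.
- Direct comparison of 90% with 80%, 250 facilities each: standard error √((0.09 + 0.16)/250) = 0.0316, z = 3.16, power Φ(3.16 − 1.96) ≈ 88%. Simulation: 90%.

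Simulated detection (in-person response 95%; trait prevalence 50% except in the fourth row, where 70% of facilities are in the 80% group):

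| Phone response by trait | Planned balance test | Responders vs non-responders, original 500 |
|---|---|---|
| 95% vs 85% | 0.4% | 97% |
| 90% vs 80% | 1.2% | 90% |
| 85% vs 75% | 2.5% | 82% |
| 92% vs 80% | 1.3% | 94% |
| 95% vs 75% | 44% | 100% |
| 95% vs 65% | 98% | 100% |
| 90% vs 80%, trait defines strata, fully refilled | 0% | 88% |
| 95% vs 75%, trait defines strata, fully refilled | 0% | 100% |

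In the scenarios simulated, about 380 to 444 of 500 facilities were common to both samples.

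**3. Response-rate test.** Take 95% in person, 92% by phone, correlation 0.4.
- Unpaired standard error: √((0.95 × 0.05 + 0.92 × 0.08)/500) = 0.0156.
- Discordant proportions b = 0.052 and c = 0.022. Paired standard error: √((b + c − (b − c)²)/500) = 0.0121. Ratio 1.28.
- Power 48% unpaired against 69% paired. At 95% vs 90%, 91% against 97%. At 95% vs 80%, about 100% for both. At zero correlation the two agree.
- True size of the unpaired test when rates are equal: 5.0%, 2.8%, 1.1% and 0.2% at correlations 0, 0.2, 0.4 and 0.6.

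**4. Does the follow-up regression run?** Either test can open it.
- 30% of facilities remote, phone response 80% remote and 92% otherwise, in-person 96%: overall phone response 0.3 × 0.80 + 0.7 × 0.92 = 88.4%, gap 7.6 points, unpaired standard error 0.0168, z = 4.5. The response-rate test opens the regression in about 99.5% of studies.
- Phone 97% vs 90% by trait (93.5% overall), in-person 95%: the response-rate test is significant in 17% of runs and the balance test in 0%; the direct comparison detects the selection in 91%.
- Phone 97% vs 87% by trait (92% overall), in-person 92%: 4.4% and 0.3%; the direct comparison detects it in 99%.

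**The case against.** **The test may be meant as paired.** The article says only that the t-test is simple. A one-sample t-test on 500 facility-level differences would fit those words and would closely match McNemar's test. A reader might infer that an independent-samples test is prescribed; the text does not say so, and a condensed article may leave it to the analysis plan. This stands: the fair statement is that the pairing is not used in what is written. The Data analysis section's announcement of a paired sample does not settle it, because that sample holds only facilities that took part in both surveys, where response is 100% by definition. Even if the test is run unpaired, the error is conservative under positive correlation and immaterial for a large gap.

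**The regression is a safeguard.** A reader might infer that a failed balance test means the follow-up regression will not be triggered. The documents do not support that: a significant response-rate difference is enough, and the protocol expects phone non-response to be higher. This stands too. The regression is missed mainly when overall rates are similar while phone response is selective. Its wording is a separate weakness: confined literally to discordant facilities, its binary outcome does not vary.

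**The balance test answers another question.** Whether the two achieved samples resemble each other is a legitimate question, and the test need not be dropped. But resemblance after refilling says little about who failed to answer.

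**It is not blind to everything.** Replacement is made only where a facility is available. Table 2 takes all 15 Dushanbe facilities, 41 City and 53 District Health Centers, so losses there cannot be refilled from the same group and would remain visible. Gaps of 20 to 30 points on other traits are detected in 44% to 98% of runs.

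**Conclusion.** The point holds as a should-fix. As planned, the balance test is very conservative and has roughly 0-3% power for a 10- to 12-point selective gap in phone response, against about 80-97% for the direct comparison in the original 500. A non-significant balance test cannot be read as absence of selective phone non-response. The loss from an unpaired response-rate test is smaller and conditional: it matters for gaps of a few points with positive within-facility correlation.

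All response rates, correlations and trait prevalences are assumptions. The conservatism of the balance test does not depend on them closely, since it follows from the overlap whenever both surveys reach most of the original facilities. The documents do not support the broader claims that the test can detect no selection at all or that the regression will generally stay unrun.

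**What to change.** Work on the original 500 facilities, before replacement.

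1. State that response rates are compared with a paired method: McNemar's test, or the paired difference with its 95% confidence interval. Compare dropout among facilities that started both interviews, since dropout is not defined for a facility that never started.
2. Add a comparison of responders with non-responders, separately for each survey, on sampling-frame characteristics, and make this the test of selective non-response. Keep the comparison of the two final samples as description only.
3. Run the discordance regression whatever the earlier tests show, among all facilities that completed the in-person survey, so that the outcome can take both values.

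The cost is a few sentences and slightly more analysis, using frame data and non-response records that the study will hold. Data collection does not change.
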